## Abstract

**Background:**

Labor, although natural and physiological, is a period that can be marked by stress, pain, anxiety, suffering, fear, and anguish for a woman. Thus, non-pharmacological methods that reduce pain during labor are important to allow a better experience without the use of medications. Therefore, the aim of this study is to evaluate the effects of non-pharmacological pain relief methods, added or not to the application of transcutaneous electrical stimulation (TENS), on pain, satisfaction with the childbirth, duration of labor, and newborn conditions.

**Methods:**

This is a randomized controlled clinical trial, with a non-probabilistic convenience sample, composed of women in the first active stage of labor, admitted to a public institution. The parturients will be divided into 3 groups: group 1 (*n* = 36) composed of parturients who will have continuous support and will be encouraged to walk, adopting different positions with the use of the Swiss ball and receiving back massage for 30 min; group 2 (*n* = 36) composed of parturients who will also have continuous support and will be encouraged to walk, adopt different positions using the Swiss ball, and will receive the application of TENS for 30 min; and group 3 (*n* = 36) composed of parturients who will have continuous support and will be encouraged to walk, adopting different positions with the use of the Swiss ball, and will receive placebo TENS application for 30 min. The outcomes evaluated in the study will be pain intensity assessed by the visual analog scale of pain applied before, immediately after, and 30 min and 1 h after the interventions; Experience and Satisfaction with Childbirth Questionnaire (QESP) applied 12 to 24 h after delivery; and data regarding delivery (type of delivery, total duration of labor, and possible obstetric complications) and neonate (weight, height, possible complications, Apgar score in the first and fifth minutes).

**Discussion:**

With this research, it is expected to understand the effects of the intervention through TENS electrostimulation added to other non-pharmacological methods for pain management during labor.

**Trial registration:**

Brazilian Registry of Clinical Trials (REBEC) RBR-68kh6j. Registered on March 17, 2020

## Administrative information

Note: the numbers in curly brackets in this protocol refer to SPIRIT Checklist item numbers. The order of the items has been modified to group similar items (see http://www.equator-network.org/reporting-guidelines/spirit-2013-statement-defining-standard-protocol-items-for-clinical-trials/).

## Introduction

### Background and rationale {6a}

Labor, although natural and physiological, is a period of time that can be marked by stress, pain, anxiety, suffering, fear, and anguish for women [1]. Thus, the World Health Organization (WHO) recommends the use of non-pharmacological pain relief methods such as walking, kinesiotherapy or maternal mobility, exercise on a Swiss ball, massage, breathing exercises, relaxation techniques, and hot bath with the aim of reducing pain and promoting an active posture of the parturient, with greater autonomy for women [2].

Non-pharmacological methods of pain relief can be used alone or together with the multidisciplinary team (physiotherapists, nurses, nursing technicians, doctors, and doulas), depending on the parturient’s choice and the hospital’s infrastructure [3–6]. Some studies have demonstrated the effectiveness of walking and massage in reducing pain and increasing pain tolerance during labor [7–9]. Besides that, studies with other methods such as breathing and relaxation techniques, maternal mobility, Swiss ball exercises, and hot bath have observed a decrease in the use of medications, a decrease in anxiety and stress, a decrease in the duration of the active phase of labor, and greater body perception of the parturient [10–12].

A non-pharmacological method that has been investigated is the use of transcutaneous electrical stimulation (TENS). It is an equipment used for pain relief, and studies have analyzed its effect during labor [13, 14]. There are two theories that explain the action of TENS in reducing pain. The first is the theory proposed by Melzack and Wall in 1965 that explains the action of TENS through the gate control theory. Thus, TENS provides electrical stimulation through the skin, through sensory stimuli that will carry information to the brain through afferent fibers to the dorsal horn of the Aß medulla [15, 16]. Therefore, there is a blockage of pain impulses to the brain, as this fiber transmits the information faster than the fibers responsible for transmitting pain [15, 16]. Another theory is explained by the release of endogenous opioids by the brain, such as beta-endorphins, which have an analgesic effect [15, 16].

For the use of TENS during labor, the electrodes are placed at the level of the T10–L1 and S2–S4 vertebrae [14, 17]. During application, the parturient reports tingling or tickling, without causing muscle contraction or pain. Studies have shown the safety of the method for the mother and fetus and positive effects during labor such as reduced pain, anxiety, labor duration, and use of complementary analgesia and improved satisfaction [13–19].

Despite the number of studies on the use of TENS in labor and its wide use in clinical practices, systematic reviews on the subject show the low quality of studies so far [18, 20]. Thuvarakan et al. [20], in a meta-analysis, found only a small efficacy of TENS in reducing pain intensity during labor. It is not possible to say whether the results were affected by the low quality of the studies or not.

Furthermore, the reality of clinical practice is the use of non-pharmacological methods of pain relief together with an attempt to provide greater relief to women. However, the current scientific evidence comes mainly from studies that evaluated the isolated effects of the techniques [12]. Therefore, it is important to analyze the possible additional effect of using TENS in addition to other non-pharmacological pain relief methods through a clinical trial with greater methodological control. These results can contribute to the clinical practice of the physiotherapists in obstetrics, justifying or not the investment in equipment in maternity hospitals.

### Objectives {7}

The aim of this randomized clinical trial is to verify the effects of non-pharmacological methods of pain relief added to the application of TENS on pain, satisfaction with childbirth, duration of labor, and the birth conditions of newborns.

### Trial design {8}

This is a single-blind randomized controlled superiority trial to compare the three groups randomized in parallel (1:1:1). This article has been written in accordance with the Standard Protocol Items: Recommendations for Interventional Trials (SPIRIT) guidelines.

## Methods: participants, interventions, and outcomes

### Study setting {9}

The trial will be carried out at the Hospital Municipal Modesto de Carvalho, in the city Itumbiara, GO, Brazil.

### Eligibility criteria {10}

Patients eligible for inclusion in the trial must meet all the following criteria:
Pregnant women in active laborLow-risk pregnanciesWomen with a gestational age of 37–42 weeksGestation with a single fetus in the cephalic position

### Exclusion criteria

The following are the exclusion criteria:
Having a wound or inflammation in the cutaneous areas of application of the TENS electrodesPresence of a pacemakerInability to understand verbal commands

### Who will take informed consent? {26a}

A signed informed consent form will be obtained from each patient prior to their participation in the study. The evaluator will acquire consent during hospitalization. The evaluator will explain all steps of the study, and the volunteers who agree to participate will sign the term.

### Additional consent provisions for the collection and use of participant data and biological specimens {26b}

Not applicable. There will be no biological sample collection in this study.

### Interventions

#### Explanation for the choice of comparators {6b}

In clinical practice, non-pharmacological methods of pain relief are used together, in an attempt to promote better results. However, no studies were found in the literature that verified, through the comparison of non-pharmacological methods of pain relief already recommended by the WHO and added to the application of TENS, whether such a resource would bring a potential reduction in pain in parturients during labor. Therefore, it was decided to compare non-pharmacological methods of pain relief with the same methods added to the use of TENS and placebo.

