#### Intervention description {11a}

The intervention of the three groups will take place during the first active phase of labor, from admission, which occurs when the parturient has 4 cm of cervical dilation, until the beginning of the expulsive period. The three groups will receive continuous support from professionals, encouraging walking and the adoption of vertical postures (standard intervention). In addition, parturients in group 1 will be positioned on a Swiss ball to receive a massage in the dorsal region for 30 min. Classic massage movements will be used, such as superficial sliding, deep sliding, kneading, friction, and rolling. Almond oil will be used to facilitate manual maneuvers.

Women in group 2 will undergo a standard intervention plus an intervention using TENS electrostimulation using the portable Neurodyn equipment (IBRAMED-Indústria Brasileira de Equipamentos Médicos EIRELI, Brazil). The parturients will be positioned seated on the Swiss ball, and four silicone electrodes will be fixed with masking tape in the thoraco-lumbar region, at the levels of T10–L1 and S2–S4. A frequency of 100 Hz and a pulse width of 100μs will be used, with intensity depending on the sensitivity of each patient for 30 min [17] (Figs. 1 and 2. Women in group 3 will undergo standard intervention and placebo intervention. They will be positioned and have electrodes attached in a similar way to group 2. However, the equipment will remain with the intensity button deactivated, without current flow (Figs. 1 and 2).

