## Assignment of interventions: allocation

### Sequence generation {16a}

Participants will be randomized in a ratio of 1:1:1 to the three groups: group 1 (standard intervention and massage in lumbar region for 30 min), group 2 (standard intervention and TENS application in lumbar region), and group 3 (standard intervention and TENS placebo application in lumbar region for 30 min), using computer-generated random numbers.

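### Group 1 is an active massage comparator, not the same methods without TENS, so group 2 versus group 1 estimates TENS against massage; group 2 versus group 3 is the comparison that answers the added-effect question.

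*Protocol article*

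**What the plan says.** The background section {6a} gives the purpose of the trial: to "analyze the possible additional effect of using TENS in addition to other non-pharmacological pain relief methods". It adds that the results should help decide whether maternity hospitals invest in the equipment. The comparator rationale {6b} then describes the design: "it was decided to compare non-pharmacological methods of pain relief with the same methods added to the use of TENS and placebo".

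The arms are set out in Intervention description {11a}, and the Abstract and Sequence generation {16a} agree on what each group receives in addition to the common care. All three groups have continuous support and encouragement to walk and to adopt upright postures, which the protocol calls the standard intervention. The extra component of the first arm is stated thus: "parturients in group 1 will be positioned on a Swiss ball to receive a massage in the dorsal region for 30 min". For the second arm, "Women in group 2 will undergo a standard intervention plus an intervention using TENS electrostimulation". Group 3 has the standard intervention with electrodes placed in a similar way but no current. Massage is not listed for group 2 or group 3.

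The background also lists massage among the recommended non-pharmacological methods and cites studies in which walking and massage reduced labor pain. Statistical methods {20a} gives an ANOVA between the groups and names no pairwise comparison.

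**The concern.** The rationale describes an add-on design: some methods, then the same methods with TENS on top. A reader who takes it at its word will treat group 1 as the arm without TENS and read group 2 versus group 1 as the added effect of TENS. In the arms as defined, group 2 does not keep the massage and add TENS; it has TENS in place of massage.

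If massage relieves pain, as the background suggests, an effective TENS could look no better than group 1 and be reported as adding nothing. That would bear directly on the equipment question. The same comparison also lacks participant blinding to technique, which the blinding section {17a} acknowledges, and the VAS is self-reported.

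**Working it through.** **Step 1. What each arm contains** (Abstract; {11a}; {16a})

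| Group | Standard intervention (S) | Massage | TENS device |
|---|---|---|---|
| 1 | yes | yes | none |
| 2 | yes | no | active |
| 3 | yes | no | inactive |

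No arm has massage plus TENS, and no arm has S alone.

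**Step 2. Can the rationale be read so that it fits?** If its methods include massage, groups 2 and 3 do not receive the same methods as group 1. If its methods mean S only, there is no methods-alone arm, because group 1 adds massage. Neither reading makes group 1 the arm without TENS that the sentence implies.

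**Step 3. What each contrast estimates.** Let T, M and P be the pain reductions from adding active TENS, massage and sham TENS to S.

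- Group 2 minus group 1 = (S + T) − (S + M) = T − M. This equals T only if M = 0.
- Group 2 minus group 3 = (S + T) − (S + P) = T − P, which is active over sham TENS on the common background.
- Group 1 minus group 3 = M − P, which is massage against sham.

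**Step 4. Illustration.** From Sample size {14}: difference 1.5, SD 1.61, 36 per group, alpha 0.05 (taken as two-sided). The usual two-group formula with power 0.80 gives n = 2 × (1.960 + 0.842)² × 1.61² / 1.5² = 18.1, so 19 per group. The stated 36 is not reproduced. It is larger, so power at 36 exceeds 0.80. That is a separate matter and does not affect this point.

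With 36 per group, the standard error of a difference is 1.61 × √(2/36) = 0.379, and power is approximately Φ(difference / 0.379 − 1.96). Three things are assumed: T = 1.5, P = 0, and the values of M below. The documents give none of these as true effects.

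| Assumed M (cm) | Expected group 2 − group 1 (cm) | Power, 2 vs 1 | Power, 2 vs 3 |
|---|---|---|---|
| 0 | 1.5 | 0.98 | 0.98 |
| 0.5 | 1.0 | 0.75 | 0.98 |
| 1.0 | 0.5 | 0.26 | 0.98 |
| 1.5 | 0 | 0.025 (upper tail; no true difference) | 0.98 |

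**The case against.** The best defence is that the design already contains the right comparison. Groups 2 and 3 share the support, the walking, the postures, the Swiss ball and the electrode placement, and differ only in current. Anyone who reads the arm descriptions sees exactly what each woman receives, and an active massage comparator is a legitimate choice. No section tells the analyst to read the added effect from group 2 versus group 1, and the choice of pairwise contrasts is commonly left to a statistical analysis plan, which is not shown here. All of this stands. The fault is therefore not a missing contrast list but a stated comparison that the arms do not match.

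Three further limits also stand:

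- The sizes in the table come from assumed massage effects. The upper end simply equals the planned difference, so only the direction and the algebra carry evidential weight.
- A reader might infer that group 2 versus group 1 is wholly unblinded. The blinding section does not support that: the evaluator and the data processor are blind to allocation, and it is the participants who are not fully blind to technique.
- A reader might extend the contradiction to Objectives {7}. That section makes no claim of identical methods and names no comparison with group 1, so it does not conflict with the arm definitions.

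What the defence does not remove is the rationale sentence itself, which invites the wrong reading of group 1.

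**Conclusion.** The point holds. The comparator rationale misdescribes the arms, and group 2 versus group 1 estimates TENS against massage. It gives the added effect of TENS only if massage has no effect; otherwise it falls short of T by exactly M, whose size the documents do not give. This conclusion rests on the arm definitions alone and needs no assumed effect size.

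A reader might go further and infer that the trial cannot show an added effect of TENS. The documents do not support that. Group 2 versus group 3 isolates active over sham TENS on the shared standard intervention. Two limits apply to that contrast: it measures the effect over sham (T − P), and it says nothing about adding TENS to massage, because no arm combines them.

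**What to change.** Before the data are analysed:

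- Reconcile the comparator rationale {6b} with Intervention description {11a}, so that it no longer says the same methods are given with and without TENS.
- Name group 2 versus group 3 as the comparison that answers the added-effect question in the background {6a}, and state that it concerns active over sham TENS on the standard intervention.
- Describe group 1 as an active massage comparator, and state that group 2 versus group 1 is interpreted only as TENS versus massage, with participants not blinded to technique.

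The cost is a few sentences and one pre-specified contrast. Treatment, enrolment and data collection do not change.

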#### Intervention description {11a}

The intervention of the three groups will take place during the first active phase of labor, from admission, which occurs when the parturient has 4 cm of cervical dilation, until the beginning of the expulsive period. The three groups will receive continuous support from professionals, encouraging walking and the adoption of vertical postures (standard intervention). In addition, parturients in group 1 will be positioned on a Swiss ball to receive a massage in the dorsal region for 30 min. Classic massage movements will be used, such as superficial sliding, deep sliding, kneading, friction, and rolling. Almond oil will be used to facilitate manual maneuvers.

Women in group 2 will undergo a standard intervention plus an intervention using TENS electrostimulation using the portable Neurodyn equipment (IBRAMED-Indústria Brasileira de Equipamentos Médicos EIRELI, Brazil). The parturients will be positioned seated on the Swiss ball, and four silicone electrodes will be fixed with masking tape in the thoraco-lumbar region, at the levels of T10–L1 and S2–S4. A frequency of 100 Hz and a pulse width of 100μs will be used, with intensity depending on the sensitivity of each patient for 30 min [17] (Figs. 1 and 2. Women in group 3 will undergo standard intervention and placebo intervention. They will be positioned and have electrodes attached in a similar way to group 2. However, the equipment will remain with the intensity button deactivated, without current flow (Figs. 1 and 2).

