### Outcomes {12}

#### Primary outcome measure

The primary outcome measure is change in the visual analog scale (VAS) from baseline to immediately after the intervention. The VAS is a simple one-dimensional instrument, used worldwide to assess pain intensity. It is characterized by a 10-cm-long horizontal line, where 0 represents no pain and 10 the worst imaginable or severe pain. They will be evaluated before the intervention and immediately after the intervention. All measurements will be performed in the period between uterine contractions.

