### Participant timeline {13}

Initially, volunteers will be numbered to avoid the risk of being identified. Soon after admission to the hospital, they will answer the standard anamnesis composed of questions about gynecological, obstetric, and health history, lasting approximately 10 min.

Before starting the intervention, the volunteer will be asked to mark the intensity of her pain at the moment on the VAS line. Immediately after and 30 min and 1 h after the interventions with the use of massage, TENS, or placebo, the request for pain intensity indication will be repeated.

After 12 to 24 h after the end of delivery, the volunteer will be visited by the researcher in the rooming-in and will be instructed to answer the intensity of pain in the VAS at this time, in addition to answering the QESP questionnaire. Then, birth and newborn data will be collected from the medical records.

The schematic diagram of the participant’s timeline can be seen in Fig. 3.

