### Recruitment {15}

Participants will be recruited at the Modesto de Carvalho Municipal Hospital, in the city Itumbiara, GO, Brazil. This hospital has an average of 67 births per month, with a rate of vaginal birth around 43.51%. No advertising is allowed for recruitment, and no inducements will be given to recruit patients into the study.

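### No latest session start is set, so women who start late cannot give the later in-labor VAS scores; for the primary VAS change, stage of labor adds noise rather than bias

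*Protocol article*

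**What the plan says.** - **Window.** Intervention description {11a} sets the intervention of all three groups "from admission, which occurs when the parturient has 4 cm of cervical dilation, until the beginning of the expulsive period".
- **Entry.** Eligibility criteria {10} require active labor, low risk, term, and a single cephalic fetus, and give no dilation range. The abstract describes a sample "composed of women in the first active stage of labor, admitted to a public institution". Implementation {16c} randomizes every consenting woman who meets the inclusion criteria.
- **Session.** In group 1 the women "receive a massage in the dorsal region for 30 min"; TENS and placebo TENS also last 30 min.
- **Primary outcome.** This is "change in the visual analog scale (VAS) from baseline to immediately after the intervention".
- **Later scores.** Participant timeline {13} asks for pain intensity "Immediately after and 30 min and 1 h after the interventions with the use of massage, TENS, or placebo". The 30-min and 1-h scores are secondary, as is one taken 12–24 h postpartum.
- **Condition on readings.** "All measurements will be performed in the period between uterine contractions".
- **Allocation and analysis.** "Participants will be randomized in a ratio of 1:1:1 to the three groups", with no stratification stated. Section {20a} names ANOVA for parametric data. Section {20c} says missing data will be described by group and multiply imputed if necessary.

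**The concern.** The window in {11a} permits session starts that the schedule in {12} and {13} cannot follow through labor. For such a woman, a later score would be missing, taken in the expulsive period, or taken after birth, when there are no longer contractions to measure between. The article does not say which applies.

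Two things are at stake.

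1. **Losses tied to an outcome.** Whether a later score can be obtained depends on how fast labor goes. The Background cites studies in which TENS, and other non-drug methods, shortened labor, and Objectives {7} make labor duration an outcome. If one arm shortens labor, it loses more later scores among its fastest women. Randomization does not protect against that. Imputing an in-labor pain score for a woman who has already delivered has no clear meaning.
2. **Precision.** If pain change over 30 min varies with stage of labor, a wide spread of stages at the start adds variance to the primary outcome. With 36 per arm and no stratification, it also allows chance imbalance.

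**Working it through.** **Time needed, from {11a}, {12} and {13}, counted from session start**

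- Primary score: about 30 min.
- 30-min score: 30 + 30 = 60 min.
- 1-h score: 30 + 60 = 90 min.

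A start less than 90 min before the expulsive period rules out a first-stage 1-h score. Less than 60 min also rules out the 30-min score. Less than 30 min means that the session, and so the primary score, cannot be completed in the first stage. This follows from the text without assumptions.

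**How many women (illustration only)**

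The documents do not give the distribution of start times. Assume starts evenly spread over a first stage of T minutes. The share too late is then minutes needed / T. Progress of 1 or 0.5 cm/h over 6 cm (4 to 10 cm, assumed) gives T = 360 or 720; T = 180 is a shorter assumed case.

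| T (min) | Session (30/T) | 30-min score (60/T) | 1-h score (90/T) |
|---|---|---|---|
| 180 | 17% (6 of 36) | 33% (12 of 36) | 50% (18 of 36) |
| 360 | 8% (3 of 36) | 17% (6 of 36) | 25% (9 of 36) |
| 720 | 4% (1.5 of 36) | 8% (3 of 36) | 12.5% (4.5 of 36) |

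Even spread is unfavorable to the plan. If every session began soon after admission at 4 cm, covering the remaining 6 cm in 1.5 h would take 6/1.5 = 4 cm/h, and losses would be far smaller.

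**Effect on the primary comparison**

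Sample size {14} gives difference 1.5, SD 1.61, alpha 0.05 (two-sided assumed), power 0.80 and 36 per group. The usual two-mean formula gives n = 2 × [1.61 × (1.960 + 0.842)/1.5]² = 18.08, so 19 per group. The stated 36 is not reproduced. That is a separate matter and errs toward a larger trial.

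Power at 36 per group comes from a two-sample t-test with noncentrality 1.5/(SD × √(2/36)). At SD 1.61 this is 3.95, and power is about 97%. Now add an assumed SD from stage of labor, with total SD = √(1.61² + added²):

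| Added SD | Total SD | Power, alpha 0.05 | Power, Bonferroni for 3 pairs |
|---|---|---|---|
| 0 | 1.61 | 97% | 93% |
| 0.5 | 1.69 | 96% | 90% |
| 1.0 | 1.90 | 91% | 82% |
| 1.5 | 2.20 | 81% | 67% |
| 2.0 | 2.57 | 69% | 51% |

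At alpha 0.05, power falls below 80% once total SD exceeds 1.5/[(1.960 + 0.842) × √(2/36)] = 2.27. That is an added SD of √(2.27² − 1.61²) = 1.60.

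**Share of variance explained by dilation**

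This is (slope × SD of dilation)²/1.61². An assumed slope of 0.2 VAS cm per cm and dilation SD of 1 cm give 0.04/2.592 = 1.5%. A slope of 0.6 with even spread over 4–10 cm (variance 36/12 = 3, SD 1.73) gives 1.08/2.592 = 42%. A range that wide shows that the documents do not fix the size.

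**Chance imbalance**

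With 30% late starters (assumed), the SD of the difference in their share between two arms is √(2 × 0.3 × 0.7/36) = 0.108. The 95% range is about ±21 percentage points.

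**Loss of later scores**

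The planned 36 equals the stated minimum, and no allowance for loss is stated. Applying the same difference and SD to a later score, 20% loss (28 per arm) gives 93% power and 40% loss (21 per arm) gives 84%. With Bonferroni these become 84% and 70%. Selective loss is therefore the larger worry, ahead of power.

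**The case against.** The strongest reply is that {11a} ties admission to 4 cm and that {13} puts the history soon after admission, then the baseline VAS, then the session. The window to the expulsive period may describe the continuous support and walking, with the session near its beginning. A reader might infer that the plan expressly lets women enter at any dilation. It does not. That reading is only left open, because no upper limit or latest start is written. The unfixed start is the firmer point, and it remains even if every woman is admitted at 4 cm.

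A reader might also infer that stage of labor, rather than treatment, determines the primary result. The documents do not support that either. The arms are concurrent and randomized, so stage affects all of them alike in expectation, and chance imbalance is already reflected in the standard error. The planning SD of 1.61 may already contain such a spread, in which case nothing is added to it.

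Two further replies stand in part. The later scores are secondary, and {20c} does provide for missing data, but it does not distinguish a score overtaken by birth from an ordinary missing one. Covariates are often left to an analysis plan, so plain ANOVA in the article is not an error. Adjustment is offered as an improvement. The mismatch between window and schedule belongs to the protocol.

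**Conclusion.** The concern holds in limited form. The entry criteria and intervention window permit starts from which the 1-h score, sometimes the 30-min score, and rarely the primary score cannot be obtained in the first stage. The loss depends on labor speed, so a treatment effect on labor duration could make it differ by arm.

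For the primary VAS change the consequence is extra variance and possible chance imbalance, not systematic bias. The documents do not show that the primary test is underpowered: on the stated inputs power is about 97%, and an added SD of about 1.6 would be needed to bring it below 80% at alpha 0.05. All loss, variance and imbalance figures rest on the stated assumptions about start times, progress and slope.

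**What to change.** 1. Reconcile {10} and {11a} with the schedule in {12} and {13}. State a dilation range at entry or a latest session start such that the session and the 1-h VAS fit in the first stage. The clinical team sets the value.
2. Record dilation from the last routine examination before the session. Use it as a baseline covariate (ANCOVA in place of plain ANOVA) in the VAS and labor-duration comparisons.
3. Report by arm the scores not obtained because the expulsive period or birth came first. Do not impute them as ordinary missing in-labor scores.

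**Cost.** One protocol line, one data field, one covariate and one reporting row. Some late arrivals are lost and the population is slightly narrower. Recruitment {15} states "This hospital has an average of 67 births per month" and a vaginal birth rate of 43.51%, so 67 × 0.4351 = about 29 vaginal births a month. The trial needs 108 women in 23 months (April 2020 to February 2022), or 108/23 = about 4.7 a month. The 29 is before the other eligibility and consent filters, so the real margin is smaller. By the article's own rule, a major modification needs ethics approval and a registry update. If recruitment is too far advanced for the first item, the third can still be done, and so can the second if the dilation readings are in the records.
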